### 2.14 Data presentation and statistical analysis plan

Power analyses for each primary outcome were conducted in R, using the SIMR package (Green and Macleod, 2016), which estimates power for linear mixed models by fitting a regression model multiple times under different scenarios, or simulations (100 simulations were performed for each power calculation). Effect sizes (Cohen’s d) and data (means and SDs) were obtained from prior alcohol/cannabis co-use studies (Hartman et al., 2016a) and/or prior studies conducted in our laboratory (Spindle et al., 2018; Spindle et al., 2021) that administered the proposed doses of oral/vaporized cannabis or alcohol alone. Overall, all power analyses revealed that 32 participants (16 men/16 women) in Part 1 and Part 2 would provide sufficient power (≥ 0.80 power for all 100 simulations) to test the study hypotheses stated.

For each outcome, descriptive statistics (means and standard deviations) will be generated. Linear mixed models will be used to test for differences across experimental conditions. Hypothesis tests will be two-sided, and significance will be set at *p* < 0.05. Factors entered into these models will include: Time (number of levels will differ depending on outcome variable), Alcohol Dose (0%, 0.05%, and 0.08%), Cannabis Dose (0, 10, and 25 mg Δ9-THC), and Sex (male or female). Time, alcohol dose, and cannabis dose will be within-subject factors (i.e., repeated measures); sex will be a between-subject factor. Maximum concentration (C_max_) and area under the curve (AUC) for Δ9-THC and Δ9-THC metabolites (11-OH-Δ9-THC; Δ9-THC-COOH) will be entered as covariates. Holm-Bonferroni corrections will be used to control for multiple comparisons. Data will be inspected for normality (skewness, kurtosis, outliers) and, where necessary, data transformations will be applied. Missing data is expected to be rare, as tasks and instruments are computerized, and field sobriety tasks will be video recorded. Additionally, if a participant presents elevated concentrations of Δ9-THC or Δ9-THC metabolites at baseline, and these values do not increase following active drug administration, this participant will be excluded from analysis.

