For Part 1 and Part 2, a priori planned comparisons will be conducted to compare mean peak change-from-baseline scores for each outcome for: (1) alcohol alone (BAC 0.05%) to alcohol with cannabis (BAC 0.05% + 10 mg Δ9-THC and 25 mg Δ9-THC); and 2) cannabis alone (10 mg Δ9-THC and 25 mg Δ9-THC) to cannabis with alcohol (BAC 0.05% + 10 mg Δ9-THC and 25 mg Δ9-THC). Additionally, planned comparisons will compare impairment (e.g., DRUID scores, composite drive scores) between cannabis with alcohol (BAC 0.05% + 10 m g Δ9-THC and 25 mg Δ9-THC) to the positive control condition (alcohol alone: BAC 0.08%). Correlations will be conducted to assess the relations between DRUID and driving performance. Sensitivity and specificity analyses will be conducted to characterize the effectiveness of the DRUID for determining driving impairment. Specifically, we will plot the sensitivity (true positive rate) and specificity (true negative rate) of the DRUID at identifying impaired driving by comparing various DRUID cutoffs to established cutoffs for driving simulator data that are indicative of clinically meaningful impaired driving in real-world settings (e.g., SDLP change-from-placebo ≥ 2.4 cm; Jongen et al., 2016). Sensitivity and specificity will be calculated as follows: sensitivity (100 × [TP/(TP + FN)]) and specificity (100 × [TN/(TN + FP)]).

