This study was designed to maintain a high degree of scientific rigor and experimental control, while also providing ecologically valid and generalizable data. Participants will complete 7 double-blind, double-dummy outpatient sessions where they will administer placebo or active cannabis (10 or 25 mg Δ9-THC) and a placebo drink or alcohol drink calculated to produce a BAC of 0.05%; there is also a positive control session with placebo cannabis and alcohol at a target BAC of 0.08%. The double-dummy design in which participants always receive both an experimental beverage (containing alcohol or placebo) and cannabis (active or placebo) will help control for expectancy effects for both drugs. The within-subject crossover design where participants serve as their own control will greatly reduce variability due to individual differences in drug metabolism, sensitivity, and other factors, and increase statistical power. The cannabis doses were informed based on our prior research (Vandrey et al., 2017; Spindle et al., 2018; Spindle et al., 2021), which showed that 10 mg Δ9-THC elicits discriminable drug effects but little to no impairment while 25 mg Δ9-THC reliably impairs cognitive/psychomotor performance. Thus, these two doses are ideal for testing the sensitivity of the various performance measures in this study. Moreover, these Δ9-THC doses are ecologically valid, as they are common among retail cannabis products sold in dispensaries (Hammond, 2021). Target BACs were selected based on *per se* limits for alcohol in most U.S. states (0.08%) and most of Europe (0.05%). Dosing participants to a 0.05% BAC in alcohol and cannabis co-use conditions will also avoid ceiling effects on study outcomes and mitigate potential untoward drug effects (e.g., emesis) that may be present if higher alcohol doses were given with cannabis. This study design will also reveal whether alcohol (at a BAC below the U.S. legal limit for DUI) and oral/vaporized cannabis have additive or synergistic effects when combined that meet or exceed the effects produced by alcohol alone at a higher BAC (0.08%) that does constitute DUI. Lastly, the proposed timing of cannabis and alcohol administration will ensure that peak cannabis effects (for both oral and vaporized cannabis) coincide with peak alcohol effects, thus capturing the “worst-case scenario” in terms of impairment from alcohol/cannabis co-use for both routes of administration.

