Overall, this project can improve public safety, including by informing various regulatory decisions regarding cannabis. First, this project can inform impairment detection standards for alcohol and cannabis. For example, should alcohol/cannabis co-use (at a 0.05% BAC) produce additive or synergistic impairment that is commensurate with impairment from alcohol alone at a 0.08% BAC (the current *per se* limit for impairment in the United States), these results would suggest a lower *per se* limit may be needed for those who have co-used alcohol and cannabis. In addition, this project will further evaluate a novel cannabis impairment detection tool (the DRUID) that has shown promise in preliminary research (Spindle et al., 2021). Further enhancement of this instrument could improve public safety because there are currently no empirically validated methods for identifying impairment from cannabis. Second, results can assist regulators faced with future decisions regarding the allowance of commercial establishments that sell alcohol and cannabis or products that contain both alcohol and Δ9-THC. Finally, this study will provide key insights that will be critical to relay to the general public such as: 1) differences in the magnitude, onset, and duration of driving impairment from oral and vaporized high Δ9-THC cannabis, 2) the extent to which cannabis impairment is augmented when co-used with alcohol, and 3) the relation between one’s perceived level of cannabis impairment versus their objective level of impairment. Ultimately, given the unprecedented and growing number of people with legal access to cannabis, communicating information related to cannabis-induced impairment *via* mass media campaigns or other accessible channels will be critical to mitigating cannabis-related harms.

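### The article promises to show whether co-use meets 0.08% alcohol impairment, but the only test stated for that contrast is a two-sided difference test, which cannot support that claim

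*Protocol article*

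**What the plan says.** Section 2.14 sets the inferential frame for every outcome: "Linear mixed models will be used to test for differences across experimental conditions", and "Hypothesis tests will be two-sided, and significance will be set at *p* < 0.05". Holm-Bonferroni correction is added. After the planned comparisons of co-use with each drug alone, the section adds that "planned comparisons will compare impairment (e.g., DRUID scores, composite drive scores) between cannabis with alcohol" (0.05% BAC with 10 mg or 25 mg Δ9-THC) and alcohol alone at 0.08%. For this last comparison it gives no direction, margin or interval rule.

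Section 3 (Comments) states what the comparison is for. The design is to reveal whether the two drugs "have additive or synergistic effects when combined that meet or exceed the effects produced by alcohol alone at a higher BAC (0.08"% is the level named there). Later the section considers that co-use at 0.05% might "produce additive or synergistic impairment that is commensurate with impairment from alcohol alone at a 0.08% BAC", and continues: "these results would suggest a lower *per se* limit may be needed for those who have co-used alcohol and cannabis".

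**The concern.** Exceeding 0.08% alcohol is a superiority question, and a two-sided difference test answers it. Meeting 0.08%, or being commensurate with it, is a similarity or non-inferiority question. It needs a statement of how large a shortfall would still count as meeting, and evidence that a larger shortfall is excluded. Section 2.14 supplies neither. If the test is not significant, the stated analysis leaves the question open, although the data may be compatible with co-use being clearly less impairing than 0.08% alcohol. What is at stake is the conclusion with the most direct regulatory use in the article, the suggestion of a lower legal limit for people who co-use.

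**Working it through.** **The plan's own figure.** Section 2.14 states that 32 participants per part give at least 0.80 power. It names the sources of its effect sizes and SDs but prints no values, so the figure cannot be reproduced. It can be back-solved for a simple paired contrast, in units of the SD of the within-person differences. With two-sided alpha 0.05 and 80% power, the detectable difference is (1.960 + 0.842)/√32 = 0.495 SD by the normal approximation, and 0.51 SD by the noncentral t with 31 df.

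**Inputs for the check.** From section 2.14: n = 32 per part, within-subject design, two-sided alpha 0.05. Assumed, because the article gives no figures: the true shortfalls, the margins and the SDs. They are shown as ranges.

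**Precision.** The 95% CI half-width is t(0.975, 31)/√32 = 2.040/5.657 = 0.361 SD.

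**Chance of a non-significant result when co-use truly impairs less than 0.08% alcohol.** This is 1 − power from the noncentral t with 31 df and noncentrality (shortfall × √32). The last column is the first Holm step if the family is only the two co-use doses.

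| True shortfall (SD) | Noncentrality | Non-significant, alpha 0.05 | Non-significant, alpha 0.025 |
|---|---|---|---|
| 0.2 | 1.13 | 80% | 88% |
| 0.3 | 1.70 | 62% | 73% |
| 0.4 | 2.26 | 41% | 53% |
| 0.5 | 2.83 | 22% | 32% |

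Correction for multiplicity makes a finding of no difference more likely, so it gives no protection against a wrong similarity claim.

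**Illustration on a scale the article uses.** Section 2.14 cites a 2.4 cm SDLP change from placebo as a cutoff for the DRUID analysis. It is not a margin against 0.08% alcohol. If the true shortfall were 2.4 cm and the SD of differences 4, 6, 8 or 10 cm (assumed), the standardised shortfall would be 0.6, 0.4, 0.3 or 0.24, and the test would be non-significant 9%, 41%, 62% or 74% of the time.

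**What a margin-based test could do with n = 32.** Non-inferiority of co-use to 0.08% alcohol, one-sided 0.025, true difference zero, fixed margin:

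| Margin (SD) | Power at n = 32 | n for 80% power (normal approximation) |
|---|---|---|
| 0.2 | 19% | 197 |
| 0.3 | 38% | 88 |
| 0.4 | 59% | 50 |
| 0.5 | 78% | 32 |
| 0.6 | 91% | 22 |

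At a margin of 0.5 SD and one-sided 0.0125 (first Holm step for two doses), the power is 68%.

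**A margin defined as half the 0.08% effect.** Write C for co-use, A for 0.08% alcohol and P for placebo. The condition C − A > −½(A − P) rearranges to C − ½(A + P) > 0. That is one contrast, and it carries the uncertainty in A − P. With equal correlations between sessions its variance is proportional to 1 + ¼ + ¼ = 1.5, against 2 for a paired difference, so its SD is √(1.5/2) = 0.866 of the paired SD. If the 0.08% effect is 1.0 SD (assumed) and C = A, the standardised effect is 0.5/0.866 = 0.577 and the power at n = 32 is 89%.

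**The case against.** Several points on the other side stand.

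- A reader might infer that the authors intend to read p > 0.05 as commensurate. Nothing in the article says so, and section 2.14 also promises means and SDs for each outcome. The gap is the lack of a valid route to the claim, not a declared misuse of the test.
- A reader might infer that noisy or insensitive outcomes would favour the policy conclusion. The sentence in section 3 also requires additive or synergistic impairment, and section 2.14 plans difference tests of co-use against each drug alone. An insensitive outcome tends to fail those. This was simulated with n = 32, assumed effects of 0.5, 0.4, 0.9 and 1.2 SD for 0.05% alcohol, cannabis, co-use and 0.08% alcohol, and additive taken to mean that co-use beats each drug alone at p < 0.05. The chance of finding co-use additive and not different from 0.08% was about 40% at full sensitivity, 10% at half and 0.3% or less at none. The 40% is a residual risk, since co-use was set truly below 0.08%, but it falls as sensitivity falls.
- A reader might infer that the positive control is never set against placebo. Alcohol dose enters the mixed model at 0%, 0.05% and 0.08%, so that contrast can be estimated. It is only absent from the named planned comparisons.
- The policy text is hedged discussion, the primary aim is to characterise impairment, and a condensed article may leave a margin to a fuller plan.

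The last point softens the finding but does not remove it. The article itself states the type of test, its sidedness, the alpha, the contrast and the inference, and these do not fit together.

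**Conclusion.** The point holds as a mismatch within the article. Section 3 promises an answer on whether co-use meets 0.08% alcohol, and attaches a regulatory suggestion to commensurate impairment. Section 2.14 gives only a difference test, which supports exceeds or falls short and nothing in between. With 32 people the 95% interval extends 0.36 SD of the paired differences either side, so shortfalls of 0.3 to 0.4 SD would be missed in 62% to 41% of trials. These figures rest on a simple paired contrast, complete data and assumed shortfalls.

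It might also be inferred that the similarity question is answerable at the planned size. The documents do not support that, because they give neither a margin nor an SD. Under a fixed margin, power reaches 78% only if that margin is as wide as about 0.5 SD, and it falls quickly below that.

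**What to change.** In section 2.14:

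1. For a named outcome, such as the Composite Drive Score (higher is worse), report the 95% CI for co-use minus 0.08% alcohol. Claim meets or commensurate only if the lower limit lies above minus a margin fixed before unblinding. If the margin is half the 0.08% effect, test the single contrast of co-use minus one half of (0.08% + placebo), so that the uncertainty in that effect is counted.
2. Claim exceeds only if the lower limit of co-use minus 0.08% alcohol is above zero.
3. Name 0.08% alcohol against placebo, already estimable from the planned model, as a planned contrast that must first show impairment on that outcome.
4. State that a non-significant difference supports neither claim.

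If no margin can be justified, withdraw the wording on meeting 0.08% and on commensurate impairment from section 3, and report the interval only.

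The cost is one or two named contrasts, one margin to justify and a few sentences, with no new data collection. The similarity claim becomes harder to make, and its power at 32 participants depends on the margin chosen.

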## 3 Comments

Controlled human laboratory studies are a valuable method for developing a detailed understanding of the acute impairment profile of alcohol, cannabis, and co-use of both substances. However, studies on alcohol and cannabis co-use are scarce and the few that have been conducted have typically administered smoked cannabis. Oral and vaporized cannabis products are increasing in popularity and these alternative forms of cannabis may produce stronger and/or more prolonged effects compared with smoked cannabis. However, there is presently limited data on the acute effects of co-use of alcohol and oral/vaporized cannabis, and the one study previously published on alcohol and vaporized cannabis co-use showed a significant increase in Δ9-THC and its metabolites in the combined drug condition versus cannabis alone (Hartman et al., 2015). This two-part randomized crossover clinical laboratory study will extend prior research by characterizing the acute impairing effects of alcohol and oral and vaporized high Δ9-THC cannabis, both alone and together, across multiple ecologically relevant doses. Assessments include a state-of-the-art driving simulator, a battery of field sobriety tests and cognitive and psychomotor performance tasks, and subjective drug effect instruments.

This study was designed to maintain a high degree of scientific rigor and experimental control, while also providing ecologically valid and generalizable data. Participants will complete 7 double-blind, double-dummy outpatient sessions where they will administer placebo or active cannabis (10 or 25 mg Δ9-THC) and a placebo drink or alcohol drink calculated to produce a BAC of 0.05%; there is also a positive control session with placebo cannabis and alcohol at a target BAC of 0.08%. The double-dummy design in which participants always receive both an experimental beverage (containing alcohol or placebo) and cannabis (active or placebo) will help control for expectancy effects for both drugs. The within-subject crossover design where participants serve as their own control will greatly reduce variability due to individual differences in drug metabolism, sensitivity, and other factors, and increase statistical power. The cannabis doses were informed based on our prior research (Vandrey et al., 2017; Spindle et al., 2018; Spindle et al., 2021), which showed that 10 mg Δ9-THC elicits discriminable drug effects but little to no impairment while 25 mg Δ9-THC reliably impairs cognitive/psychomotor performance. Thus, these two doses are ideal for testing the sensitivity of the various performance measures in this study. Moreover, these Δ9-THC doses are ecologically valid, as they are common among retail cannabis products sold in dispensaries (Hammond, 2021). Target BACs were selected based on *per se* limits for alcohol in most U.S. states (0.08%) and most of Europe (0.05%). Dosing participants to a 0.05% BAC in alcohol and cannabis co-use conditions will also avoid ceiling effects on study outcomes and mitigate potential untoward drug effects (e.g., emesis) that may be present if higher alcohol doses were given with cannabis. This study design will also reveal whether alcohol (at a BAC below the U.S. legal limit for DUI) and oral/vaporized cannabis have additive or synergistic effects when combined that meet or exceed the effects produced by alcohol alone at a higher BAC (0.08%) that does constitute DUI. Lastly, the proposed timing of cannabis and alcohol administration will ensure that peak cannabis effects (for both oral and vaporized cannabis) coincide with peak alcohol effects, thus capturing the “worst-case scenario” in terms of impairment from alcohol/cannabis co-use for both routes of administration.

The proposed study population was also carefully considered. The cannabis-use criteria of study participants (i.e., ≤ 2 uses/week but ≥ 5 uses in the past year) will constrain the impact of Δ9-THC tolerance on behavioral outcomes while ensuring that participants are not inexperienced with cannabis. Participants will be required to report two recent binge drinking episodes and to have co-used alcohol and cannabis at least once in the past year; these criteria will further increase the external validity of this study, as binge drinkers and co-users are highly likely to report driving under the influence of cannabis and/or alcohol (Metrik et al., 2018; Patrick et al., 2018). The binge drinking criteria will also ensure that study participants can tolerate the two alcohol doses. Non-drinkers and people under the age of 21 will not be included for ethical and legal reasons. Those meeting criteria for severe AUD will not be eligible to limit potential study confounds (e.g., these individuals would likely have greater alcohol tolerance and complications with withdrawal during abstinence). Overall, the study population is ideal for: safely administering the proposed alcohol and cannabis doses and reducing the likelihood of adverse effects or untoward drug effects, maximizing our ability to detect impairment, and increasing generalizability of our findings to individuals most likely to co-use these drugs and drive while impaired.

A key reason we decided to write this protocol paper was to use this as a platform to describe the custom driving scenarios we created for this project and to share the drives with researchers interested in using them. Though there have been many well-designed and informative prior studies on simulated driving impairment from alcohol, cannabis, or other drugs, there has historically been little standardization across experiments and laboratories with respect to the types of driving simulations tested. The considerable heterogeneity of driving simulations used in prior research often makes it difficult to compare outcome measures across studies. Beyond having few publicly available driving simulation examples, another notable hindrance to conducting driving simulator research is the lack of tools to facilitate data extraction and organization. For example, the STISIM software collects data every 0.1 s (10 Hz), generating thousands of lines of data for each completed drive. Oftentimes there is a need to examine a particular outcome measure at a specific driving segment (e.g., SDLP during a divided attention task, reaction time to a stimulus), which requires the creation of complex programs to extract, calculate, and organize the data appropriately; few, if any, of these programs are publicly available to researchers. For this project, using the STISIM coding language, we created 10 unique, yet comparable, driving simulations (each about 25 min in duration) that test key aspects of performance shown to be impacted by cannabis and alcohol. We have shared these drives (see Methods) along with a custom an R script that can extract and organize the data into an excel spreadsheet. These simulations require participants to navigate various environments (e.g., residential, rural, and metro areas) where they interact with signal lights, stop signs, and respond to unexpected events (e.g., pedestrians crossing the street); data is collected at specific events of interest that may be impacted by alcohol/cannabis intoxication. These drives also include two controlled driving scenarios (car following task and divided attention task) demonstrated to be sensitive to alcohol/cannabis effects. The 10 versions of the driving simulation were created to mitigate practice/learning effects and differ only by the order that events/scenarios occur and by the type of accident avoidances the driver must respond to. We encourage any researchers interested in using these drives to contact us in the interest of promoting cross-study comparisons and future collaborations.

There are several alternate design options beyond the scope of this project that may be worth exploring in future studies. For example, this study will only administer cannabis that contains high Δ9-THC concentrations and low concentrations of CBD and other cannabinoids. Additional studies are needed to understand how other cannabis chemotypes (e.g., high CBD/low Δ9-THC) interact with alcohol. Moreover, additional studies are needed to understand how cannabis impairment differs in older populations (over 55 years old) or those with more frequent (e.g., daily) cannabis use patterns than the target sample for this research. Lastly, though the use of a driving simulator is safe and provides excellent experimental control, it likely cannot fully capture the complexity of actual driving. On-road studies examining the effects of alcohol and oral/vaporized cannabis will be an important follow-up to this research.

Overall, this project can improve public safety, including by informing various regulatory decisions regarding cannabis. First, this project can inform impairment detection standards for alcohol and cannabis. For example, should alcohol/cannabis co-use (at a 0.05% BAC) produce additive or synergistic impairment that is commensurate with impairment from alcohol alone at a 0.08% BAC (the current *per se* limit for impairment in the United States), these results would suggest a lower *per se* limit may be needed for those who have co-used alcohol and cannabis. In addition, this project will further evaluate a novel cannabis impairment detection tool (the DRUID) that has shown promise in preliminary research (Spindle et al., 2021). Further enhancement of this instrument could improve public safety because there are currently no empirically validated methods for identifying impairment from cannabis. Second, results can assist regulators faced with future decisions regarding the allowance of commercial establishments that sell alcohol and cannabis or products that contain both alcohol and Δ9-THC. Finally, this study will provide key insights that will be critical to relay to the general public such as: 1) differences in the magnitude, onset, and duration of driving impairment from oral and vaporized high Δ9-THC cannabis, 2) the extent to which cannabis impairment is augmented when co-used with alcohol, and 3) the relation between one’s perceived level of cannabis impairment versus their objective level of impairment. Ultimately, given the unprecedented and growing number of people with legal access to cannabis, communicating information related to cannabis-induced impairment *via* mass media campaigns or other accessible channels will be critical to mitigating cannabis-related harms.
